### **12.10.2 Study Discontinuation Criteria**

If the clinical investigation has to be discontinued, each subject will be treated as described above.

The sponsor has the right to terminate this clinical investigation, e.g. for the following reasons:

- Serious, insolvable problems with the quality of the data
- Unforeseeable circumstances at the investigational sites, which require discontinuation of the study
- Unacceptable risks

- New scientific or medical knowledge

## **13 SAFETY EVALUATION AND REPORTING**

### **13.1 DEFINITIONS**

#### **13.1.1 Adverse Event (AE) (ISO 14155)**

Any untoward medical occurrence, unintended disease or injury, or any untoward clinical signs (including an abnormal laboratory finding) in subjects, users or other persons, whether or not related to the investigational medical device.

This includes events related to the investigational device or the comparator and those related to the procedures involved.

For users or other persons this is restricted to events related to the investigational medical device.

#### **13.1.2 Adverse Device Effect (ADE) (ISO 14155)**

Adverse event related to the use of an investigational medical device.

This definition includes adverse events resulting from insufficiencies or inadequacies in the instructions for use, the deployment, the implantation, the installation, the operation, or any malfunction of the investigational medical device.

This includes any event that is a result of a use error or intentional misuse.

#### **13.1.3 Device Deficiency (ISO 14155)**

Inadequacy of a medical device with respect to its identity, quality, durability, reliability, safety or performance, such as malfunction, misuse or use error and inadequate labeling.

#### **13.1.4 Serious Adverse Event (SAE) (ISO 14155)**

Adverse event that,

- led to death,
- led to serious deterioration in the health of the subject, that either resulted in
  - a life-threatening illness or injury, or
  - a permanent impairment of a body structure or a body function, or
  - in-patient or prolonged hospitalization, or
  - medical or surgical intervention to prevent life-threatening illness or injury or permanent impairment to a body structure or a body function,
- led to foetal distress, foetal death or a congenital abnormality or birth defect.

Planned hospitalization for a pre-existing condition, or a procedure required by the clinical investigation plan (CIP), without serious deterioration in health, is not considered a serious adverse event.

#### **13.1.5 Serious Adverse Device Effect (SADE) (ISO 14155)**

Adverse device effect that has resulted in any of the consequences characteristic of a serious adverse event.

### **13.1.6 Unanticipated Serious Adverse Device Effect (USADE) (ISO 14155)**

Serious adverse device effect, which by its nature, incidence, severity or outcome has not been identified in the current version of the risk analysis report.

Anticipated: an effect, which by its nature, incidence, severity or outcome has been previously identified in the risk analysis report. According to the Instruction for use (2016), it is most important not to inhale when applying the spray since this may cause transient asthma-like symptoms, such as coughing and hoarseness; the study subjects will be instructed accordingly (see 10.2).

### **13.1.7 Incidents (MPSV)**

According to the Ordinance on Medical Devices Vigilance (MPSV), an incident is a malfunction, failure or a modification of the features or performance or an inaccurate label or instruction manual for a medical device, which directly or indirectly caused, may have caused in the past, or may cause in the future, death or a serious aggravation of the state of health of a patient, a user or another person.

## **13.2 DOCUMENTING AND REPORTING ADVERSE EVENTS, ADVERSE DEVICE EFFECTS AND DEVICE DEFICIENCIES**

### **13.2.1 Documenting Adverse Events and Adverse Device Effects by the Investigator**

During all examinations, the investigator records any observed AEs and those reported by subjects upon questioning.

If an AE occurs, the seriousness, relationship (not related, unlikely, possible, probable and causal relationship) to the investigational device, time of occurrence and duration of the observed AE, treatment and resolution/outcome will be recorded in the study documentation. All necessary measures are to be taken to determine the cause of the AE and its possible connection to the study.

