## **10.6 BLINDING**

In this single-blind study, the subjects, the study site staff handling the IP and the study monitors will not be blinded to treatment assignment. The investigator performing the cold symptom assessment at V2, the project manager, the statistician and all further study team members will be blinded to treatment assignment.

The unblinded site study staff and the monitor(s) will take utmost care not to unblind the investigator performing the cold symptom assessment at V2 or any further blinded study team members at any occasion during the entire study duration.

The subjects will be instructed not to unblind the investigator.

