### **12.2 VISIT 2 (V2), 1– 3 DAYS AFTER SYMPTOM START**

- Questioning and documentation of possible occurrence of AEs/device deficiencies
- Questioning and documentation of new or changed concurrent treatment
- Review of the diary by a study team member (except investigator)
- Assessment and documentation of cold
- Checking criteria for further participation
- Physical examination
- Measurement of blood pressure and pulse rate

Between V1 and V2, the study site will have monthly phone contact with the subjects as a reminder about the study.

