### **13.2.2 Documenting and Reporting Device Deficiencies and Incidents by the Investigator**

During all examinations after applying the investigational product, the subjects will be asked about any device deficiencies observed. If a device deficiency is reported, the deficiency including the assessment if it may be regarded as an incident will be recorded in the study documentation.

Reportable are all device deficiencies that might have led to a serious adverse event if

- a) suitable action had not been taken, or
- b) intervention had not been made or
- c) if circumstances had been less fortunate, as well as any incidents.

The reporting is handled under the SAE reporting system and will be reported as specified in the form "Report on device deficiencies" (*"Bericht über Mangel des Medizinproduktes / Vorkommnis"*, in the ISF) immediately after becoming aware (but not later than 3 calendar days) to the sponsor and the CRO.

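### The V2 questioning on adverse events and device deficiencies conflicts with the investigator blind: a spray-linked report can reveal the arm before the cold assessment, or may be held back

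*Protocol*

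**What the plan says.** **Who is blinded.** Section 10.6 says: "The investigator performing the cold symptom assessment at V2, the project manager, the statistician and all further study team members will be blinded". By contrast, the subjects themselves and "the study site staff handling the IP and the study monitors will not be blinded to treatment assignment". Two duties protect the blind. Unblinded staff and monitors must guard it for the whole of the study, and for subjects the rule is "The subjects will be instructed not to unblind the investigator". Neither duty has an exception for safety reports, and neither ends once the V2 assessment is done.

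**Who collects safety data.** Section 13.2.1 names the investigator: "During all examinations, the investigator records any observed AEs and those reported by subjects upon questioning". For each event it requires the "relationship (not related, unlikely, possible, probable and causal relationship) to the investigational device" to be recorded. Section 13.2.2 is headed "Documenting and Reporting Device Deficiencies and Incidents by the Investigator", and its text says "During all examinations after applying the investigational product, the subjects will be asked about any device deficiencies observed".

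**Order of steps at V2.** The first item in section 12.2 is "Questioning and documentation of possible occurrence of AEs/device deficiencies". The cold assessment comes later in the list. The investigator is excluded from the diary review but not from this item.

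**Dispensing.** Section 10.4 has the investigator hand the product to the subjects.

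**The concern.** The comparison group receives no product, so only a verum subject can say that the spray caused a cough or that the pump failed. Such a statement to the blinded investigator identifies the arm. Two outcomes are possible, and each has a cost.

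- **The subject speaks.** The investigator then judges whether the symptoms are a common cold while knowing the arm. Under section 12.7.1 that judgement feeds the percentage of subjects with prevention of cold outburst, which is a main endpoint. It is also the one assessment for which the investigator blind was set up.
- **The subject stays silent, or leaves the spray out of the account.** The event is then missed at V2, or recorded without its link to the device. Adverse events and device deficiencies are named safety parameters in section 7.2.

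**Working it through.** No figure in the plan can be reproduced here, so the check is a comparison of sections.

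1. **Is the person who collects the reports the person who must stay blind?** Section 10.6 blinds the investigator who does the V2 assessment. Section 13.2.1 has the investigator record events at every examination, and V2 is one. The same term is used throughout, and no sentence gives the safety questions to someone else. For device deficiencies the link is weaker: it rests on the heading of 13.2.2, because its text and the list in 12.2 are in the passive.

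2. **Does the conflict depend only on what subjects say?** No. The relationship to the device must be recorded on five levels. An investigator who does not know whether the subject had the device cannot use that scale meaningfully.

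3. **Did the protocol handle the same problem elsewhere?** Yes, for the diary. Sections 12.2, 12.3 and 12.7.1 keep the investigator away from it. There is no matching exclusion for the safety questions.

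4. **Can a spray effect be told from the cold?** Sections 6.2 and 13.1.6 name coughing and hoarseness after inhaling the spray. Cough is also one of the eight Jackson symptoms in 12.7.1. A cough reported without mention of the spray can therefore be put down to the cold.

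5. **Visit timing.** Use of the product lasts at most 12 days (10.2). V2 falls on day 1 to 3 after symptom start (12.2), apart from a documented weekend or holiday delay. V3 falls on day 16 ± 4, that is, day 12 to day 20 (12.3). V2 is therefore the one visit expected to fall within the period of use. A report not made at V2 waits between 12 − 3 = 9 and 20 − 1 = 19 days for the next visit. The instruction to subjects still applies then, although no blinded cold assessment remains.

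6. **Can the loss be sized?** Only by assumption. Take 200 × 1/2 = 100 verum users, an assumed proportion p with a spray reaction by V2, and an assumed share s of those who say nothing. The chance that V2 records no reaction is (1 − p(1 − s))^100.

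| p | s = 0 | s = 25% | s = 50% | s = 75% |
|---|---|---|---|---|
| 3% | 0.048 | 0.103 | 0.221 | 0.471 |
| 5% | 0.006 | 0.022 | 0.080 | 0.284 |

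The protocol gives neither p nor s, and the formula ignores the second questioning at V3. The spread, from about 2% to 47% once any silence is assumed, shows that the result is set by the assumptions. It is not an estimate of lost safety data.

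**The case against.** A reader might infer that a verum subject is forced either to break the blind or to conceal a harm, and that the safety results are therefore biased towards no harm. The documents do not support that much, for five reasons.

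- **Section 10.6 blinds a role.** Sections 15.4 and 17.2 allow sub-investigators and delegates, so a site could have someone else put the safety questions. This stands as possible practice. It does not cure the text, because this task is not named as delegated and 13.2.1 names the investigator.
- **An adverse event can be reported without naming the spray.** This stands, and it limits the conflict to device defects and to events that the subject links to the spray. What is then lost is the link to the device, not necessarily the event.
- **Nothing tells subjects to withhold safety information, and they are asked directly.** Loss of the blind is at least as plausible as loss of a report. The direction of the damage cannot be fixed from the protocol.
- **Other contacts exist.** There are unblinded staff, a daily record of product use, return of the spray at V3, repeat questioning at V3, and a global safety rating by verum subjects. These soften the problem, but none is stated to be a route for spray-related reports at V2, and a four-point rating does not record events.
- **Adverse device effects and deficiencies can arise only in the verum group, and the analysis is exploratory.** No between-group comparison of them exists to be biased. Under-recording would show as a low count in one arm.

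**Conclusion.** The contradiction is in the text and goes beyond missing detail. If sections 10.6, 12.2, 13.2.1 and 13.2.2 are followed as written, a spray-linked report at V2 either discloses the arm before a judgement used in a main endpoint, or may be held back or stripped of its link to the device. Which of the two happens, and how often, cannot be estimated from the protocol. A forced concealment of harm, or a demonstrated bias in the safety results, is not shown. The conclusion rests on two readings: that the investigator in 13.2.1 is the one blinded in 10.6, which the uniform wording supports, and that the heading of 13.2.2 assigns the deficiency questions. Without the second reading, the conflict over adverse events in 13.2.1 remains.

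**What to change.** - **12.2:** Have a designated unblinded site staff member ask about adverse events and device deficiencies at V2. This can be the staff who handle the product. It can be the diary reviewer only if the protocol states that this person is unblinded: 12.2 says merely that the reviewer is not the investigator, and 10.6 blinds all team members it does not exempt. Pass spray-related reports to the investigator for causality rating only after the V2 cold assessment is signed.
- **10.6:** For each subject, end both the instruction to the subject and the staff's duty towards that investigator once the assessment is signed. Both must end, because the staff duty now runs for the whole study and would forbid the hand-over. Keep the blind for the other blinded team members. State that the instruction never restricts safety reporting to unblinded staff.
- **13.2.1 and 13.2.2:** Align them with this order and say who asks, who records and who rates causality.
- **10.4:** Reconcile the sentence that has the investigator hand out the product with the blinding in 10.6.

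The cost is amendment wording and a changed order of steps at V2. Unblinded product-handling staff are already part of the plan. There are two small downsides: causality is rated slightly later in the visit, and the investigator is unblinded for that subject after V2.

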### **13.2.2 Documenting and Reporting Device Deficiencies and Incidents by the Investigator**

During all examinations after applying the investigational product, the subjects will be asked about any device deficiencies observed. If a device deficiency is reported, the deficiency including the assessment if it may be regarded as an incident will be recorded in the study documentation.

Reportable are all device deficiencies that might have led to a serious adverse event if

- a) suitable action had not been taken, or
- b) intervention had not been made or
- c) if circumstances had been less fortunate, as well as any incidents.

The reporting is handled under the SAE reporting system and will be reported as specified in the form "Report on device deficiencies" (*"Bericht über Mangel des Medizinproduktes / Vorkommnis"*, in the ISF) immediately after becoming aware (but not later than 3 calendar days) to the sponsor and the CRO.

### **13.2.3 Reporting Serious Adverse Events by the Investigator**

All serious adverse events that occur for any reason during the study, will, even when the cause is not connected to the use of the device, be reported by the investigator as specified in the form "Report on serious adverse event" ("*Bericht über schwerwiegende unerwünschte Ereignisse*", in the ISF) within 24 hours of awareness to the sponsor and the CRO.

### **13.2.4 Safety Evaluation and Reporting by the Sponsor**

The sponsor is responsible for the ongoing safety evaluation of the clinical investigation, reviewing of the device deficiencies, incidents and SAEs reported by the investigator and any further reporting to the Ethics Committee (EC) and the Competent Authority as appropriate.

## 14 STATISTICS

### 14.1.1 Objective of the clinical investigation

The main goal of this single (investigator)-blind, randomized, parallel-group pilot clinical investigation is to evaluate the use of various assessments of common cold symptoms for proof of efficacy of CMS016317, by observed magnitude of treatment effects. For details on all end-points, please refer to section 7.

### 14.1.2 Statistical hypothesis

The present study is principally intended as an exploratory pilot study. Therefore, explorative data analyses shall be performed, including the calculation of known descriptive statistical quantities for the varied scaled variables under investigation. No prospectively specified statistical hypotheses will be proved, but possibly generated statistical hypotheses from the fore-cited descriptive analyses; the subsequent statistical tests are therefore only to be understood as exploratory ones, i.e. without any confirmative generalization of the results.

### 14.1.3 Statistical methods

All end points as well as the concurrent and safety variables will receive an explorative examination and will be descriptively assessed. For the metric data (continuous data) the statistical characteristics will be given (number, mean, standard deviation, median, extremes, quartiles). For ordinal data (discrete data) number, median, interquartile range and extremes will be calculated. If found suitable, ordinal data will be considered as supplementary metric data. For all nominal data the frequency distribution will be presented in frequency tables. The values of metric data can be merged in ordinal classes according to clinical criteria to determine their frequency distribution. Explorative estimation for the structural consistency of the groups regarded will be proved by a descriptive comparison of demographic data, values at screening and secondary (further) endpoints.

In case of generated statistical hypotheses from the above defined descriptive analyses, the subsequent exploratory statistical tests are as follows (for reasons of small samples and/or potentially non-normal distributions):

- Mann-Whitney-U test for comparison independent groups,
- Paired Wilcoxon test for the pre-post comparison within groups,
- Chi-Square test for the comparison of frequencies for independent groups.

All p-values from statistical tests are to be understood as exploratively. That means, the results may deliver interesting insights in the underlying object of research, but those findings don't qualify for a confirmative generalization. Because of the exploratory character of the study no adjustment for multiple testing will be accomplished.

The FAS population will consist of all randomized subjects for which at least one data point after onset of cold symptoms is available, and, for verum group only, who received at least one dose of IP upon onset of cold symptoms. The VCAS population will consist of subjects from FAS without any major violations of the CIP. The assignment to the study populations will be performed before unblinding and start of analysis.

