### 7.1 EFFICACY PARAMETERS

Main endpoints:

Evaluation of various assessments of common cold symptoms by the observed magnitude of treatment effects:

- Sore Throat Scale
- Irritated Throat Scale
- Jackson scale – total score, local symptoms, systemic symptoms, 2-item score (sore throat & malaise)
- WURSS-21 QoL subscore
- Percentage of subjects with prevention of cold outburst

Further endpoints [SEP]

- Duration of common cold symptoms
- Use of concomitant treatment / remedies
- Global evaluation of efficacy by subjects at study end

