### **10.5 METHODS OF RANDOMISATION AND BLINDING**

The clinical investigation will be conducted in a single-blind randomised manner. The subjects will be randomised at the screening visit. The randomisation list will be provided to the sponsor's assigned responsible person (not involved in the study) by the statistician responsible for generation of the randomisation list. The ratio of randomisation between the "IP group" (IP, and optional care as needed) and the "peer-group" (optional care only, no IP) will be 1:1. Random numbers will be assigned to the subjects in a sequential order based on time of random-

isation at each investigational site (several whole blocks will be allocated to each centre). Randomisation list will be concealed to the investigational sites. It will be stored under lock and key by the sponsor until database closure. After database closure and sign-off of the statistical analysis plan, the sponsor's responsible person will provide the randomisation list to the project manager at the CRO and the statistician responsible for the statistical analysis. The study allows for stratification with respect to centres (sites).

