#### **14.1.6 Statistical analysis plan/report**

Before database closure, a statistical analysis plan (SAP) will be provided, presenting planned statistical analyses as well as any possible deviations or additions of the data analyses originally defined in the CIP before clinical study start. Changes in the planned statistical methods and analyses after approval of the SAP will be documented in the clinical study report. The results of the statistical analyses of the study will be documented in the statistical report. The statistical report will provide the basis for the preparation of the study report.

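### Between-arm tests are triggered by the descriptive results of the same data, so p-values for picked comparisons do not hold at their nominal level, and endpoints that generate no hypothesis go untested

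*Protocol*

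**What the plan says.** Protocol 14.1.2 declares the study an exploratory pilot: "No prospectively specified statistical hypotheses will be proved, but possibly generated statistical hypotheses from the fore-cited descriptive analyses". Section 14.1.3 first has every endpoint described, then lists the tests (Mann-Whitney between groups, paired Wilcoxon within groups, chi-square for frequencies) under this condition: "In case of generated statistical hypotheses from the above defined descriptive analyses, the subsequent exploratory statistical tests are as follows". It does not say what makes a descriptive result generate a hypothesis.

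The same section limits how the results may be used. "All p-values from statistical tests are to be understood as exploratively", the protocol says, and "those findings don't qualify for a confirmative generalization". It adds: "Because of the exploratory character of the study no adjustment for multiple testing will be accomplished".

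Two passages set the timing. Under 14.1.6, "Before database closure, a statistical analysis plan (SAP) will be provided, presenting planned statistical analyses". Under 10.5, "After database closure and sign-off of the statistical analysis plan, the sponsor's responsible person will provide the randomisation list" to the CRO project manager and the analysing statistician.

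Section 7.1 names the main endpoints: the Sore Throat Scale, the Irritated Throat Scale, four Jackson scores ("Jackson scale – total score, local symptoms, systemic symptoms, 2-item score (sore throat & malaise"), the WURSS-21 QoL subscore and the percentage with prevention of a cold. That makes eight. Sections 7.1 and 14.1.1 judge these assessments by the size of the treatment effect observed on them.

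**The concern.** A Mann-Whitney or chi-square p-value is computed for a comparison that was chosen without regard to the arm difference in the data being tested. Sections 14.1.2 and 14.1.3 set out a different sequence: describe, generate a hypothesis, then test it on the same subjects. If the hypothesis arises because an arm difference looked large, the null distribution used for the test no longer applies, because small differences have been filtered out before testing.

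This matters for the trial's own aim, which is to learn which symptom assessments can show an effect of the device. Under the written rule some assessments may carry a p-value and others none, and whether an assessment gets one depends on its own result. A p-value obtained this way makes a chance difference look better supported than it is, and a later trial could take that assessment as its endpoint. The descriptive statistics listed in 14.1.3 include no between-arm estimate or confidence interval, so an untested endpoint would lack those as well.

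**Working it through.** The protocol states no alpha, power or error rate, and 14.1.5 says that the 200 subjects were not derived statistically. There is no planned figure to reproduce.

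**Inputs from the protocol**
- Candidate main endpoints: K = 8 (7.1).
- Allocation 1:1 (10.5) and 200 subjects analysed (synopsis), so about 100 per arm.
- No adjustment for multiplicity (14.1.3).

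**Assumptions, not in the protocol**
- Two-sided alpha of 0.05 (critical value 1.96).
- No true effect on any endpoint.
- Standardised test statistics approximately normal, with common correlation rho.
- A selection rule, varied below.

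**1. Timing.** By-arm descriptives need the randomisation list. It is released after SAP sign-off (10.5). A hypothesis generated from by-arm descriptives is therefore generated after the SAP is signed.

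**2. Rule A: test the endpoint with the largest difference.** The test rejects when max|Z| over the eight exceeds 1.96.
- Independent endpoints: 1 − 0.95^8 = 0.337.
- Correlated endpoints: Z_k = √rho·G + √(1 − rho)·E_k, with G and E_k independent standard normal, 500,000 draws.

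| rho | False-positive rate | Multiple of 5% |
|---|---|---|
| 0 | 33.7% | 6.7 |
| 0.5 | 25.0% | 5.0 |
| 0.7 | 19.1% | 3.8 |
| 0.8 | 15.8% | 3.2 |
| 0.9 | 11.9% | 2.4 |

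The Jackson total and its subscores share items. A model that builds them from shared items, with assumed item correlations from 0.1 to 0.6, gives 25.3% down to 18.3%, which is inside this range.

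**3. Rule B: test an endpoint only if its |Z| exceeds a threshold c (c below 1.96).** P(reject given tested) = 0.05 / P(|Z| > c).
- c = 0.5: 0.05 / 0.617 = 8.1%.
- c = 1: 0.05 / 0.317 = 15.8%. With 100 per arm, c = 1 is a standardised difference of 1 × √(2/100) = 0.14.
- c = 1.28: 0.05 / 0.201 = 24.9%.

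**4. Rule C: test the largest difference in the device's favour, still with a two-sided p-value.** For K = 8 the rate is 18.2% at rho 0, 12.6% at 0.5, 9.5% at 0.7 and 6.0% at 0.9.

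**5. Rule D: every endpoint generates a hypothesis and is tested.** Each test has its nominal 5%.

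**6. What fixing the comparisons changes.** The largest of eight statistics passes 1.96 exactly when at least one of the eight does. The Rule A rates are therefore also the chance of at least one p < 0.05 when all eight are tested without adjustment. With fixed comparisons each p-value has 5% error, while the chance of at least one p < 0.05 stays at about 12% to 34% (rho 0.9 to 0). The difference is that all eight results are then reported, not only the picked one.

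**The case against.** The strongest reply is that the protocol is open about what these tests are. It calls every p-value exploratory, declines multiplicity adjustment and rules out confirmatory use. No declared error rate is breached, because none is declared. That stands, and it limits the harm to how the p-values are read and how the assessments are compared. It does not remove the point. The disclaimers restrict generalisation and waive adjustment for the number of tests. Neither deals with a test that is run because of the result it then tests.

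A second reply is that all endpoints are described in any case, and that assessments are judged by observed effect size, not by p-values. This also stands in part: flat endpoints stay visible in the descriptives, and ranking eight scales by observed effect carries a risk of chance findings that no testing rule removes.

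Three stronger readings are tempting, and the protocol does not support them.
- A reader might infer that error rates are inflated by some fixed minimum factor. The protocol gives no alpha, selection rule or correlations, and the rate runs from 5% per test upwards depending on what is assumed.
- A reader might infer from the timing that the tests cannot be in the SAP, so the problem is unavoidable. Hypotheses taken from by-arm results cannot be there, but 14.1.6 lets the SAP make additions. It could name a test for every endpoint in 7.1 before unblinding. The SAP is not at hand, so whether it did so is unknown.
- A reader might multiply the count by the daily diary values and arrive at far higher rates. No section calls for between-arm tests day by day.

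**Conclusion.** The point holds for the protocol as written. Sections 14.1.2 and 14.1.3 state a rule under which between-arm tests follow from descriptive results in the same data. The p-value of a picked comparison is then not valid at its nominal level, even as an exploratory p-value, and endpoints that generate no hypothesis are described but not tested.

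The size is conditional. If the largest of eight null differences were picked and tested at an assumed two-sided 0.05, the false-positive rate would be roughly 12% to 34% (rho 0.9 to 0) instead of 5%. Picking only in the device's favour, or with a lenient threshold, gives less; testing every endpoint gives 5% per test. The change is worth making because 7.1 already names the endpoints, so nothing is gained by leaving the tests conditional. It is not evidence that the analysis was in fact run this way.

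**What to change.** In 14.1.3, replace the conditional sentence that introduces the tests with wording such as:

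> For each of the eight main endpoints in section 7.1, one between-group comparison, on one summary per subject fixed in the SAP before the randomisation list is released, will be performed and reported with an effect estimate and confidence interval, whatever the descriptive results show. Comparisons chosen after by-group results are known will be labelled post hoc.

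Amend 14.1.2 (and the matching synopsis text under Biometry) to agree. If the SAP already fixes these comparisons, bring the protocol into line with it. The exploratory status and the absence of multiplicity adjustment can stay, and post hoc comparisons may still carry p-values as long as they are labelled.

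The cost is a few sentences in the protocol and the corresponding SAP entry, with no extra subjects, visits or data. The small downside is that all eight results are reported, including flat ones. The change restores the 5% error per test; it does not lower the chance of at least one p < 0.05 among the eight, so the report should still read the eight results together.
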